### Interventions

Patients in the treatment group will take a daily bath using MSS for a period of 4 months. To ensure the proper application of MSS, dermatologists will advise patients to first moisten their entire body with warm water, then apply 8 g of the product (4 g per press) to the skin surface. Massage gently for 3 to 5 min to ensure full absorption, and followed by rinsing with warm water. Patients in the control group will also take a daily bath using MSS placebo for a period of 4 months. The MSS placebo was formulated to be devoid of any Chinese herbal constituents, containing only the base excipients. It was manufactured by the same entity to guarantee perfect consistency with the active treatment in all physical attributes—appearance, weight, color, odor, and packaging. The guidance and application of MSS placebo in the control group will be identical to that for the treatment group.

In this study, both of patients in the treatment group and control group will receive the same foundational therapeutic regimen. The foundational therapies include desonide cream for mild AD and triamcinolone acetonide cream for moderate AD, both of which will be applied twice daily for 2 weeks. Additionally, all patients will receive urea ointment twice daily for 4 weeks. In this study, no additional treatment is permitted, and emergency interventions require documentation in detail and will result in the withdrawal of participation.

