#### Secondary outcomes

The secondary outcome indicators include the EASI, Visual Analogue Scale (VAS), Investigator’s Global Assessment (IGA), and Dermatology Life Quality Index (DLQI) (23, 24). These indicators will be assessed at baseline (week 0) and subsequently at weeks 1, 2, 4, and 16. A detailed study schedule is presented in Table 1, which specifies the evaluation time points for each measure.

**Table 1 tab1:** Study schedule of the MuShengshu clinical trial (16 weeks).

Indicator	Baseline	Follow-up			
	Visit 1 (week 0)	Visit 2 (week 1)	Visit 3 (week 2)	Visit 4 (week 4)	Visit 5 (week 16)
Informed consent	✓	–^a^	–	–	–
Demographic features	✓	–	–	–	–
Family medical history	✓	–	–	–	–
Physical examination	✓	–	–	–	–
Inclusion/exclusion criteria check	✓	–	–	–	–
Randomization	✓	–	–	–	–
EASI^b^	✓	✓	✓	✓	✓
VAS^c^	✓	✓	✓	✓	✓
IGA^d^	✓	✓	✓	✓	✓
DLQI^e^	✓	✓	✓	✓	✓
Concomitant medications	–	✓	✓	✓	✓
Adverse events	–	✓	✓	✓	✓

a Not applicable.

b EASI: Eczema Area and Severity Index.

c VAS: Visual Analogue Scale.

d IGA: Investigator’s Global Assessment.

e DLQI: Dermatology Life Quality Index.

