### VAS

Pruritus severity in patients with mild-to-moderate AD will be assessed using the validated VAS (25). This method typically employs a 10-centimeter linear scale, with one end labeled “0 points” for “no pruritus” and the other end labeled “10 points” for “severe pruritus.” Patients mark the scale according to their pruritus perception, and evaluators determine the score by measuring the distance from the marked point to the “no pruritus” end. During each visit, participants will evaluate their peak pruritus severity over the preceding 24 h using the VAS.

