### Statistical analysis

In this study, data analysis will be conducted using the SAS 9.4 statistical software. Normally distributed quantitative variables will be summarized as mean and standard deviation (SD), while skewed distributions will be represented by the median and interquartile range (IQR). For inter-group comparisons of quantitative variables with normal distribution, the Student *t*-test will be utilized, whereas the Wilcoxon rank-sum test will be applied for skewed quantitative data. Repeated measurement data will be analyzed using repeated measures analysis of variance. Categorical variables will be presented as frequencies and proportions (%), with differences between groups evaluated through chi-square tests or Fisher’s exact tests.

Data analysis in this study will follow the intention-to-treat (ITT) principle, including all randomized participants regardless of adherence to the protocol or completion of the study (28). Missing data will be addressed under the missing-at-random assumption using sequential regression multiple imputation, which estimates missing values based on regression models that consider the relationships among all other variables (29). Furthermore, analyses will be performed on both the full analysis set (FAS) and the per-protocol set (PPS), with a *p*-value of less than 0.05 (two-tailed) is viewed as statistically significant.

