For the treatment and long-term management of AD, skin barrier repair and maintenance are essential. Guidelines for AD treatment suggest that appropriate bathing can facilitate the repair of skin lesions (12, 13). Previous studies indicate that various bath solutions can efficiently restore skin barrier function and increase skin hydration (40, 41). A meta-analysis has demonstrated that traditional Chinese herbal bath solutions can effectively alleviate clinical pruritus (42). MSS, as a weakly acidic solution containing over seven core Chinese herbal components, helps inhibit inflammation and preserve skin barrier integrity (43). Numerous studies have demonstrated that the core Chinese herbal components can exert anti-inflammatory effects through three key pathways: inhibiting the release of inflammatory mediators, regulating immune cell activity, and reducing oxidative stress (44–46). By inhibit inflammation, repairing the barrier, alleviating symptoms, and expediting recovery, this herbal bath solution anticipated to substantially improve clinical outcomes in AD patients. Additionally, this study design includes foundational therapies (desonide cream for mild AD and triamcinolone acetonide cream for moderate AD) alongside rescue medication (levocetirizine tablets for severe pruritus, 1 tablet each day), ensuring that all AD patients receive standardized background care throughout the trial.

Results in this study are expected to provide new insights and approaches for the prevention and treatment of AD. To our knowledge, this study is the first clinical trial to assess the clinical efficacy and safety of a traditional Chinese medicine solution combined with foundational therapies in the treatment of mild-to moderate AD. The evaluation will be conducted through a multidimensional approach, encompassing assessments of skin lesion severity, intensity of pruritus, and overall quality of life. The results of this study will provide robust evidence for the incorporation of traditional Chinese herbal bath solutions into clinical practice as a supplementary treatment modality for AD, thereby effectively facilitate long-term management of AD. We are planned to disseminate our findings through publication in internationally peer-reviewed journals.

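### Interventions allows nothing beyond the foundational therapies, but the Discussion builds levocetirizine rescue into the design, so a rescue user's protocol status and retention are contradictory

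*Protocol article*

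**What the plan says.** All references are to the protocol article.

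- **Interventions** (background therapy): "The foundational therapies include desonide cream for mild AD and triamcinolone acetonide cream for moderate AD", plus urea ointment for everyone. No antihistamine is named. The Abstract gives the same list.
- **Interventions** (anything else): "no additional treatment is permitted, and emergency interventions require documentation in detail and will result in the withdrawal of participation".
- **Discussion**: the design is said to include the two creams "alongside rescue medication (levocetirizine tablets for severe pruritus, 1 tablet each day", with the stated purpose of "ensuring that all AD patients receive standardized background care throughout the trial".
- **VAS**: at each visit "participants will evaluate their peak pruritus severity over the preceding 24 h using the VAS".
- **Secondary outcomes**: VAS is one of four measures. "These indicators will be assessed at baseline (week 0) and subsequently at weeks 1, 2, 4, and 16". Table 1 schedules concomitant medications at weeks 1, 2, 4 and 16.
- **Statistical analysis**: intention-to-treat, "including all randomized participants regardless of adherence to the protocol or completion of the study", with multiple imputation under missing-at-random. Results are also given for a full analysis set and a per-protocol set.

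**The concern.** Both statements are current text and both describe what patients in this trial may receive. They give different answers for a patient with severe itch who takes levocetirizine: one makes the use a breach, the other makes it part of the design. No other section settles the matter.

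Relief of pruritus is a stated aim under Study design, so itch is not incidental. Rescue is given for severe itch, and itch is also what the VAS measures. Whichever rule is applied, rescue therefore bears on the outcome. If users stay, some VAS readings are taken under an anti-itch drug. If users are withdrawn, the readings after rescue are lost for a reason tied to the outcome. These are different data sets and call for different interpretation.

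This is not a detail that a condensed article has left to a fuller document. The article states two rules that disagree, and a statistical analysis plan cannot decide who may take a drug or who is withdrawn.

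**Working it through.** **Step 1. Is levocetirizine already a permitted therapy under Interventions?** No. The list there is desonide, triamcinolone acetonide and urea. The Discussion places levocetirizine next to the creams as a separate item. By the Interventions wording it is therefore additional treatment.

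**Step 2. The two sections side by side, for a patient who takes levocetirizine for severe itch.**

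| Question | Interventions | Discussion |
|---|---|---|
| Is the use allowed? | No | Yes, as rescue |
| Does the patient stay? | Withdrawn if the use is an emergency intervention; otherwise a breach with no stated consequence | Yes |
| Per-protocol status | Violator | Compliant |
| Later VAS and EASI | Missing if withdrawn | Observed, possibly on drug |

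**Step 3. Follow each column into the analysis.** In the Discussion column, the 24-hour recall window can fall wholly within a period of daily antihistamine use. In the Interventions column, a withdrawn patient remains in the intention-to-treat analysis, but values after withdrawal are imputed. Missing-at-random would require the recorded data to account for the loss. Here the trigger is severe itch, which may arise between visits and so not be captured by the last VAS: between week 4 and week 16 there are 16 - 4 = 12 weeks without a scheduled assessment. If withdrawal comes before week 4, the imputed values include the primary endpoint for that patient.

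**Step 4. The plan's own figures.** For 85% versus 50%, two-sided 0.05, 80% power and 2:1 allocation, the pooled two-proportion formula gives 40 and 20 (power 81.6%). The printed unpooled formula gives a control group of (0.85 × 0.15 / 2 + 0.50 × 0.50) / 0.35² × (1.960 + 0.842)² = 20.10. With the 10% addition, 40 × 1.10 = 44 and 20 × 1.10 = 22, an allowance of 4 + 2 = 6 patients for the week-4 endpoint. None of this depends on the rescue rule, and the conflict depends on none of it.

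**Step 5. Can an effect be sized?** That would need the rescue rate by arm and by week, the drug's effect on VAS, and the share of users on drug at a visit. The document gives none of these. As an assumption only, take 5% use on MSS, 10% to 30% on placebo, and a 2-point effect present at the visit in every user:

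| Placebo use | Placebo users (of 22) | MSS users (of 44) | Total of 66 | Shift in VAS difference, 2 × (placebo rate - MSS rate) |
|---|---|---|---|---|
| 10% | 2.2 | 2.2 | 4.4 (6.7%) | 0.1 |
| 20% | 4.4 | 2.2 | 6.6 (10.0%) | 0.3 |
| 30% | 6.6 | 2.2 | 8.8 (13.3%) | 0.5 |

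The table shows how far the answer depends on the assumed rates. If use were higher on MSS, the sign of the last column would reverse.

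**The case against.** The best defence is that the sections can be made to agree. Interventions ties withdrawal to emergency interventions, does not define them, and does not say levocetirizine is one. The ban on other treatment could mean nothing beyond what the design provides, with the drug dropped from Methods for brevity. The first part stands: it does not follow from the text that every levocetirizine user is withdrawn. The second is strained, because Methods states a closed list followed by a ban and contains no rescue provision.

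A reader might also infer four stronger things, which the document does not support.

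- *That withdrawal removes patients, mostly controls, from the analysis.* Intention-to-treat keeps them; what is lost is their later data. The imbalance rests on assumed rates, and at 10% versus 5% the expected counts are equal (2.2 and 2.2).
- *That rescue withdrawals would use up the dropout allowance.* The 10% result in Step 5 comes from chosen rates, and the allowance serves the week-4 endpoint. Losses between weeks 4 and 16 do not touch it.
- *That rescue would hide a real itch difference.* No expected VAS difference or standard deviation is given against which to judge a shift.
- *That the primary endpoint is compromised.* EASI scores excoriation, so an influence is conceivable, but the document shows no effect beyond possible missing data before week 4.

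It is fair to add that this is a single hospital, so inconsistent handling is possible but not shown, and that concomitant medications are already recorded.

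**Conclusion.** The contradiction holds. Interventions and the Discussion give incompatible statements on whether levocetirizine may be used, and hence on the user's protocol status and possibly on retention. The direct effect is on the itch VAS, a secondary outcome, and on per-protocol membership. The effect on EASI, including week-4 EASI50, is conditional on users being withdrawn and, for the primary endpoint, on withdrawal before week 4. No size or direction of bias can be given, because the rescue rate and drug effect are not in the document. On that footing this should be fixed, but it falls short of a defect that invalidates the primary analysis. The conclusion rests only on the wording of the two sections. It takes no view on which clinical rule is right.

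**What to change.** 1. Reconcile Interventions and the Discussion into one rule on rescue use and retention, and use it in the protocol, the CRF and the site instructions. State whether levocetirizine use counts as an emergency intervention. The choice of rule is for the investigators.
2. Record the dates of any levocetirizine use under the concomitant-medication item already scheduled at weeks 1, 2, 4 and 16, so that each VAS can be classed as on or off the drug within its 24-hour window.
3. Separate stopping treatment from leaving follow-up: continue to collect outcomes from anyone who stops treatment and still consents to visits, in line with the intention-to-treat principle. This limits what has to be imputed.
4. Before unblinding, state whether levocetirizine users belong to the per-protocol set, and specify a sensitivity analysis of VAS that accounts for rescue use. The method can be set in the statistical analysis plan.

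The cost is a short amendment and a small CRF addition, with no extra visits. Recruitment began in August 2025, so patients already enrolled must be checked for levocetirizine use, and the rule under which each was handled must be identified.

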### Outcomes

#### Primary outcome

The primary outcome indicator in this study is the EASI_50_ achievement rate at week 4. The EASI_50_ achievement rate is defined as proportion of patients achieving ≥50% improvement in EASI score from baseline to week 4.

The EASI score encompasses two main components: the affected body surface area (BSA) score (A) and clinical features score (B) for areas including the head and neck, trunk, upper limbs, and lower limbs (22). Component (A) evaluates the percentage of affected BSA for each area, which is scored on a scale of 0 to 6, as follows: 0 (0%), 1 (<10%), 2 (10–19%), 3 (20–49%), 4 (50–69%), 5 (70–89%), and 6 (90–100%). Component (B) assesses four critical clinical features: erythema (E), edema/papules/infiltration (I), excoriation (Ex), and lichenification (L). Each feature is scored based on severity, ranging from 0 to 3 points (0 = none, 1 = mild, 2 = moderate, 3 = severe). The overall EASI score is calculated by multiplying the product of (A) and (B) by regional weighted coefficients (ranging from 0.1 to 0.4) and summing these values across all regions. The total EASI score ranges from 0 to 72 points, with higher scores indicating greater severity. Based on the EASI score, the skin lesion condition of AD patients is categorized as mild (0–7 points), moderate (8–21 points), or severe (>21 points). In this study, the EASI score will be assessed at baseline (week 0), and at weeks 1, 2, 4, and 16.

#### Secondary outcomes

The secondary outcome indicators include the EASI, Visual Analogue Scale (VAS), Investigator’s Global Assessment (IGA), and Dermatology Life Quality Index (DLQI) (23, 24). These indicators will be assessed at baseline (week 0) and subsequently at weeks 1, 2, 4, and 16. A detailed study schedule is presented in Table 1, which specifies the evaluation time points for each measure.

**Table 1 tab1:** Study schedule of the MuShengshu clinical trial (16 weeks).

Indicator	Baseline	Follow-up			
	Visit 1 (week 0)	Visit 2 (week 1)	Visit 3 (week 2)	Visit 4 (week 4)	Visit 5 (week 16)
Informed consent	✓	–^a^	–	–	–
Demographic features	✓	–	–	–	–
Family medical history	✓	–	–	–	–
Physical examination	✓	–	–	–	–
Inclusion/exclusion criteria check	✓	–	–	–	–
Randomization	✓	–	–	–	–
EASI^b^	✓	✓	✓	✓	✓
VAS^c^	✓	✓	✓	✓	✓
IGA^d^	✓	✓	✓	✓	✓
DLQI^e^	✓	✓	✓	✓	✓
Concomitant medications	–	✓	✓	✓	✓
Adverse events	–	✓	✓	✓	✓

a Not applicable.

b EASI: Eczema Area and Severity Index.

c VAS: Visual Analogue Scale.

d IGA: Investigator’s Global Assessment.

e DLQI: Dermatology Life Quality Index.

### VAS

Pruritus severity in patients with mild-to-moderate AD will be assessed using the validated VAS (25). This method typically employs a 10-centimeter linear scale, with one end labeled “0 points” for “no pruritus” and the other end labeled “10 points” for “severe pruritus.” Patients mark the scale according to their pruritus perception, and evaluators determine the score by measuring the distance from the marked point to the “no pruritus” end. During each visit, participants will evaluate their peak pruritus severity over the preceding 24 h using the VAS.

### IGA

The IGA is a validated 6-point ordinal scale designed for the rapid evaluation of disease severity, with higher scores indicating greater severity (26). Dermatologists utilize specific criteria to assess key characteristics of skin lesions, as follows: 0 = clear (no erythema); 1 = almost clear (minimal erythema with barely perceptible edema or papules); 2 = mild (mild erythema with palpable edema or papules); 3 = moderate (moderate erythema with noticeable edema or papules); 4 = severe (severe erythema with marked edema or papules); and 5 = very severe (confluent erythema with significant edema).

### DLQI

The DLQI is a validated tool that systematically assesses impairment in health-related quality of life across six domains over the previous week (27). These domains include physiological responses, psychological well-being, family life, interpersonal relationships, work limitations, and social activities. Each of the 10 items is rated on a 4-point severity scale (0 = none, 1 = mild, 2 = severe, 3 = very severe), and the total DLQI score is derived by summing the scores for all items, resulting in a range from 0 to 30, where higher scores indicate greater impairment in quality of life.

### Adverse events

In this study, patients with mild to moderate AD will be made aware of any potential risks associated with the study prior to signing the informed consent form. Adverse events are defined as any unintended signs, symptoms, or diseases that occur following treatment and are not necessarily linked to the intervention. All adverse events will be documented accurately in the CRF. Additionally, dermatologists will provide appropriate treatment for any adverse events encountered, and both the adherence of AD patients and the occurrence of adverse events will be recorded.

### Withdraw and dropout

In accordance with the Declaration of Helsinki, all patients will be treated with respect and have the right to withdraw from the study at any time and for any reason. Patients’ personal information will be collected and kept confidential. If a patient chooses to withdraw from the study, the reason will be documented in the CRF.

### Data collection and management

Trained dermatologists will gather data utilizing a standardized CRF, which consists of five sections: (1) demographic information, including age, gender, and census registration; (2) family medical history related to AD; (3) physical examination data such as height, weight, and body mass index (BMI); (4) baseline (week 0) and follow-up scores for EASI, VAS, IGA, and DLQI at weeks 1, 2, 4, and 16; and (5) information on concomitant medications and any adverse events.

The database will be developed using Epidata 3.1 software, featuring comprehensive validation rules. Data for all 66 participants will be input using a double data entry method conducted by two independent operators. Consistency checks between the two datasets will help identify discrepancies, which will then be resolved by cross-referencing with the original CRF until complete concordance is achieved through iterative verification.

### Statistical analysis

In this study, data analysis will be conducted using the SAS 9.4 statistical software. Normally distributed quantitative variables will be summarized as mean and standard deviation (SD), while skewed distributions will be represented by the median and interquartile range (IQR). For inter-group comparisons of quantitative variables with normal distribution, the Student *t*-test will be utilized, whereas the Wilcoxon rank-sum test will be applied for skewed quantitative data. Repeated measurement data will be analyzed using repeated measures analysis of variance. Categorical variables will be presented as frequencies and proportions (%), with differences between groups evaluated through chi-square tests or Fisher’s exact tests.

Data analysis in this study will follow the intention-to-treat (ITT) principle, including all randomized participants regardless of adherence to the protocol or completion of the study (28). Missing data will be addressed under the missing-at-random assumption using sequential regression multiple imputation, which estimates missing values based on regression models that consider the relationships among all other variables (29). Furthermore, analyses will be performed on both the full analysis set (FAS) and the per-protocol set (PPS), with a *p*-value of less than 0.05 (two-tailed) is viewed as statistically significant.

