## Methods

### Study design

This randomized, double-blind, placebo-controlled trial is designed to evaluate the efficacy of MSS combined with foundational therapies in improving skin lesions and relieving pruritus in patients with mild-to-moderate atopic dermatitis (AD). The study protocol adheres to the SPIRIT (Standard Protocol Items: Recommendations for Interventional Trials) guidelines (20). A total of 66 patients with mild-to-moderate AD will be enrolled at the Shanghai Skin Disease Hospital during August 2025 and June 2026. Patients will be randomly assigned in a 2:1 ratio to either the treatment group (MSS combined with foundational therapies, *n* = 44) or control group (MSS placebo combined with foundational therapies, *n* = 22). The study flowchart is shown in Figure 1.

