### Sample size

The sample size was calculated based on the EASI_50_ achievement rate at week 4, which was defined as the proportion of patients who achieved ≥50% improvement in Eczema Area and Severity Index (EASI) score from baseline to week 4. According to preliminary observation data, we assume that the EASI_50_ achievement rate at week 4 would be 85% in the treatment group and 50% in the control group. Based on a 2:1 randomization ratio, the sample size is calculated with PASS 15.0 software. Setting a two-tailed *α* level at 0.05 and statistical power at 80%, the calculation yields a requirement of 40 patients for the treatment group and 20 for the control group. Considering a 10% dropout rate, the final enrollment target is set at 44 patients for the treatment group and 22 patients for the control group. The specific formula for calculating sample size was as follows:
$$n_{2}=\frac{\frac{p_{1}\times (1-p_{1})}{k}+p_{2}\times (1-p_{2})}{{\left(p_{1}-p_{2}\right)}^{2}}\times {\left(\mu_{\alpha /2}+\mu_{\beta }\right)}^{2},n_{1}=k\times n_{2}$$

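### With 2:1 allocation, the Student t-test and uncorrected repeated measures ANOVA for the secondary scores lean on equal-variance and sphericity assumptions that are cheap to avoid

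*Protocol article*

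**What the plan says.** The Statistical analysis section of the protocol article chooses the test by distributional shape. For normal data it reads: "For inter-group comparisons of quantitative variables with normal distribution, the Student" t-test is used, "whereas the Wilcoxon rank-sum test will be applied for skewed quantitative data". For the visit series: "Repeated measurement data will be analyzed using repeated measures analysis of variance". A p-value "of less than 0.05 (two-tailed) is viewed as statistically significant". The section names no unequal-variance version, sphericity correction, covariance structure or confidence interval.

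Under Study design, "Patients will be randomly assigned in a 2:1 ratio to either the treatment group" or the control group. Under Sample size, "the final enrollment target is set at 44 patients for the treatment group and 22 patients for the control group".

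The scores concerned are EASI, VAS and DLQI, and IGA if it is treated as quantitative. They are measured at weeks 0, 1, 2, 4 and 16. The primary outcome, the EASI50 rate at week 4, is a proportion and goes to a chi-square or Fisher test.

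**The concern.** Student's test, as distinct from Welch's, estimates one SD from both arms together. At 44 versus 22 that SD is set mainly by the treated patients. If the controls are more variable, the standard error is too small, p-values are too small and any interval built on it is too narrow. If the treated patients are more variable, the test is conservative.

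Repeated measures ANOVA pools across arms in the same way. Its univariate within-patient tests also assume sphericity, which is doubtful when the visits are 1, 1, 2 and 12 weeks apart.

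At stake are the statements on pruritus, quality of life and mean EASI. Pruritus relief is part of the trial's stated aim under Study design, and it rests on these secondary comparisons.

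**Working it through.** **1. The plan's own figure.** The printed sample size formula, with p1 = 0.85, p2 = 0.50 and k = 2, gives

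n2 = [(0.85 × 0.15)/2 + 0.50 × 0.50] / 0.35² × (1.960 + 0.842)² = (0.31375 / 0.1225) × 7.849 = 20.10.

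The pooled-variance version gives 20 controls and 40 treated. This matches the statement that "the calculation yields a requirement of 40 patients for the treatment group and 20 for the control group". The calculation concerns a proportion and involves no SD, so it is untouched by this point and says nothing about the spread of the scores.

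**2. Inputs for the t-test check.**
- From the document: n1 = 44 treated, n2 = 22 control, two-sided 5%.
- Assumed, because the document gives no SD: normal data, equal means, and control/treated SD ratio r varied over a range.

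**3. Standard error.** With the treated SD set to 1, the pooled SE relative to the true SE is

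√{ [(43 + 21r²)/64] × (1/44 + 1/22) / (1/44 + r²/22) }.

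At r = 1.5: (43 + 47.25)/64 = 1.410; × 0.06818 = 0.0961; true variance 0.02273 + 0.10227 = 0.1250; √(0.0961/0.1250) = 0.88.

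**4. Rejection rate.** Simulation with 200,000 data sets per setting. Coverage is one minus the rejection rate.

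| r | Pooled SE / true SE | Student rejects | Coverage of 95% interval |
|---|---|---|---|
| 0.5 | 1.23 | 1.7% | 98.3% |
| 0.8 | 1.08 | 3.5% | 96.5% |
| 1.0 | 1.00 | 5.0% | 95.0% |
| 1.25 | 0.93 | 6.8% | 93.2% |
| 1.5 | 0.88 | 8.4% | 91.6% |
| 2.0 | 0.81 | 11.1% | 88.9% |
| 3.0 | 0.76 | 14.1% | 85.9% |

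The Welch test stays at 4.9 to 5.1% throughout. At 40 versus 20 the Student results are almost the same (6.9%, 8.6% and 11.2% at r = 1.25, 1.5 and 2.0). At 33 versus 33 Student stays at 5.0 to 5.1% over those ratios, so the cause is the unequal allocation combined with unequal spread.

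**5. Repeated measures ANOVA, equal variances.** Inputs: visits at weeks 0, 1, 2, 4 and 16, 44 versus 22, and correlation assumed to decay as 0.7 to 0.9 per week. The group-by-visit F test without correction rejects in 6.7 to 8.6%, that is about 7 to 8% over most of the range. Greenhouse-Geisser brings it back to about 5%.

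**6. Repeated measures ANOVA, unequal variances.** Five equally spaced time points, compound symmetry (0.5) or first-order autoregressive correlation (0.7), r = 1.5. The group main effect behaves like the t-test (8.5 to 8.6%). The group-by-visit test rejects in 12.0 to 13.4% uncorrected and 9.9 to 11.0% with Greenhouse-Geisser. The correction therefore cures the sphericity problem but not the variance problem.

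**The case against.** Four arguments stand against making more of this.

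- **No SD is given.** A reader might infer from the assumed 85% versus 50% response that control scores must be the more variable. If the log EASI ratio is normal with common SD s, the raw-scale SD ratio is exp(1.036s): 1.51 at s = 0.4 and 2.29 at s = 0.8. But that model makes EASI right-skewed. In simulation at 44 versus 22 a Shapiro-Wilk test rejected normality in at least one arm in 85 to 100% of trials, and the plan sends skewed data to the Wilcoxon test. On change from baseline (assumed baseline log-SD 0.3 to 0.5) the same model gives ratios of 0.93 to 1.88. For VAS and DLQI it gives nothing. This argument stands, so the ratio must remain an assumption.
- **The null hypothesis.** If the bath solution does nothing, both arms share one distribution, variances are equal and the t-test has its 5% size. This stands too. The t-test inflation concerns equality of means with unequal spread. Interval undercoverage can still occur when the treatment works and changes the spread.
- **A single range such as 9 to 14%.** This is also tempting. For the t-test it needs SD ratios of roughly 1.5 to 3. For the ANOVA it mixes unequal variance with uncorrected sphericity. The document supports neither as a general statement.
- **Detail for the analysis plan.** An unseen plan may specify the unequal-variance version or a sphericity correction, and the article does not write the word pooled. This limits the point but does not remove it: the article names the tests, and the conventional reading of those names is the equal-variance one.

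**Conclusion.** The point holds as a conditional one on secondary analyses. The named t-test has no protection against unequal spread at 2:1. Its error rate is about 7%, 8.5% and 11% at assumed SD ratios of 1.25, 1.5 and 2.0, and about 2% at 0.5. These figures rest on normal data and on ratios that the document does not supply.

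The sphericity problem is separate and does not need unequal variances. It rests on correlation that decays with time and on the test being run uncorrected, which the article neither states nor excludes.

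It would be wrong to conclude that the trial's error rate is generally inflated or that its primary result is at risk. The EASI50 test and the sample size are not affected, and scores analysed by the Wilcoxon test fall outside these calculations.

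**What to change.** In the Statistical analysis section:

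- Name the Welch (Satterthwaite) t-test and its interval for every between-arm comparison of means, without a preliminary test of variances.
- Replace repeated measures ANOVA by a mixed model for repeated measures with unstructured covariance, Kenward-Roger degrees of freedom and visit-specific contrasts. If ANOVA is kept, apply at least the Greenhouse-Geisser correction.
- Fit covariance separately by arm only as a sensitivity analysis. With five visits each matrix has 5 × 6 / 2 = 15 parameters, and the control matrix would rest on 22 patients. A covariance common to both arms removes the sphericity assumption but still pools spread across arms, so the Welch comparisons remain useful beside it.

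The cost is analysis wording only. Standard SAS output for the two-sample t-test already includes the Welch result. If variances are in fact equal, the Welch test loses about one percentage point of power (80.9% to 80.1% in simulation).
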